### Assessments and follow-up

The schedule of study assessments is summarized in **Table 2**. Baseline evaluations: At study entry, baseline tumor assessments are documented using imaging (CT, PET/CT and/or MRI) performed within 6 weeks prior to enrollment​. This imaging serves as the reference for measuring treatment response and progression going forward. Patients also complete baseline patient-reported outcome questionnaires (PRO-CTCAE, EORTC-QLQ-C30). Baseline blood samples are drawn and banked for exploratory biomarker studies.

**Table 2 T2:** Study timeline.

Required investigation	Pre-study (prior to enrolment)	Before 1st fraction of radiation	First follow-up after radiation (4 weeks ± 2 weeks)	Subsequent follow-up (every 12 ± 2 weeks until 104 weeks)
History and physical exam				
ECOG		X	X	X
Weight		X	X	X
Radiology				
CT CAP or PET/CT	Within ≤42 d			X
CT or MRI Brain (optional)	Within ≤42 d			If indicated
Specimen collection				
Blood collection		X	X	At the time of progression
Adverse events				
Survival status			X	X
CTCAE v5.0		X	X	X
Quality of life				
PRO-CTCAE		X	X	X
EORTC-QLQ-C30		X	X	X

Treatment and follow-up visits: During radiation delivery (which spans up to two weeks), patients are seen regularly for treatment management. An acute toxicity evaluation is performed at the end of the radiation treatment course (within a week of completing radiotherapy). Thereafter, follow-up visits are scheduled at approximately 8 weeks post-radiation, and then every 3 months for the first year, or until further disease progression. At each follow-up, a clinical examination and toxicity assessment are conducted. Adverse events are graded according to NCI CTCAE v5.0. In addition, patients complete PRO-CTCAE questionnaires to capture symptoms and side effects from the patient’s perspective, and the EORTC quality-of-life questionnaires are repeated at defined intervals (e.g. 3, 6, 12 months) to assess any changes in global health status and specific symptoms over time.

Radiologic assessments (CT of chest/abdomen/pelvis, with MRI or PET as needed) are performed roughly every 12 weeks following treatment, in alignment with standard melanoma follow-up schedules, to monitor for disease progression. Responses and progression are evaluated by RECIST 1.1 criteria. Any new or growing lesions are documented. If a patient experiences progression outside the originally treated sites (i.e. new sites of disease or growth of previously stable lesions), this will be recorded as an endpoint (end of PFS), and further management (such as a change of systemic therapy) will be at the treating physician’s discretion. The protocol allows for repeat local therapy in some circumstances, but any progression beyond the initial oligoprogressive event generally signals trial completion for that patient (subsequent therapies are recorded for analysis of time to next treatment).

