**Materials/methods:**

This is an open-label, single-arm phase 2 trial. Eligible patients have metastatic melanoma with ≤10 extracranial oligoprogressive sites while on first-line systemic therapy. Oligoprogression is defined using modified RECIST 1.1 or PERCIST criteria. All oligoprogressive sites will receive SBRT per institutional guidelines, typically delivered over 3 fractions. Patients will stay on current systemic therapy. The primary endpoint is PFS defined as the time from enrollment to the date of further disease progression. Secondary endpoints include overall survival, time on current systemic therapy, out-of-field response, tolerance of SBRT, and quality of life (QOL). In addition, serial blood samples are collected for exploratory analyses of circulating tumor DNA (ctDNA), mutant allele fraction, and immune profiling (including CD8+ T-cell subsets). The trial aims to enroll 52 patients over 12 months with additional 24 months of follow-up.

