**Figure 1 f1:**
[figure not shown]
CURB-Melanoma Trial Schema.

Primary Endpoint:

Progression-free survival - defined as time from enrollment to further disease progression (assessed by modified RECIST) or death from any cause.

Secondary Endpoints:

Overall survival - defined as the time from study enrollment to death from any cause.Time on current systemic therapy before switching to second line therapy - captures the duration from initiation of the current systemic therapy to the start of second-line treatment.Toxicity - treatment-related adverse events will be assessed and graded according to CTCAE v5.0.Quality of life - patient-reported outcomes will be evaluated using validated instruments (PRO-CTCAE, EORTC-QLQ-C30).

Exploratory Endpoints:

Out of field response - defined as a new radiographic response (per RECIST 1.1) in a non-irradiated lesion that was stable at enrollment. This endpoint is hypothesis-generating, as attribution to an abscopal effect is limited by the concurrent influence of ongoing systemic therapy.Blood collection: at baseline, 4 weeks post-radiation, and at the time of progression. At each timepoint, two 10 mL Streck Cell-Free DNA Blood Collection Tubes (BCT) will be collected for future analysis of circulating tumor DNA (ctDNA), cytokines, proteomics, metabolomics, and other serum/plasma biomarkers. In addition, two 10 mL Cell Preparation Tubes (CPT) with sodium citrate will be collected for isolation of peripheral blood mononuclear cells (PBMCs) for multiplex analysis of circulating immune cells including, flow cytometry (CyTOF), T cell receptor sequencing (TCR-seq) and single-cell RNA sequencing (scRNA-seq) for a minimal volume of 40 mL.

The primary hypothesis is that adding SBRT or hypofractionated radiotherapy to oligoprogressive lesions while continuing systemic treatment will yield a clinically meaningful extension of PFS. The trial protocol has been approved by the institutional Research Ethics Board, and the study will be monitored by the center’s clinical trials unit for compliance and safety.

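### The primary PFS event is defined in two ways, and the follow-up rule leaves regrowth of an irradiated lesion outside the recorded event

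*Protocol article*

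**What the plan says.** Three places in the protocol article describe the primary event.

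- **Study design, outcomes and end-points (Primary Endpoint):** PFS is "defined as time from enrollment to further disease progression (assessed by modified RECIST) or death from any cause". No site is exempted.
- **Assessments and follow-up:** "Responses and progression are evaluated by RECIST 1.1 criteria". The event at follow-up is then given as "progression outside the originally treated sites (i.e. new sites of disease or growth of previously stable lesions), this will be recorded as an endpoint", and a parenthesis equates this with the end of PFS. The same section adds that "Any new or growing lesions are documented", that "The protocol allows for repeat local therapy in some circumstances", and that "any progression beyond the initial oligoprogressive event generally signals trial completion for that patient".
- **Abstract, Materials/methods:** "The primary endpoint is PFS defined as the time from enrollment to the date of further disease progression". Again there is no restriction by site.

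**The concern.** The intervention is radiotherapy to the progressing lesions, and its stated aim is to eliminate resistant disease so that the systemic drug can go on working elsewhere. Regrowth of an irradiated lesion is therefore a failure of the intervention itself. A primary endpoint that left it out would credit the treatment with time in which the treatment had already failed.

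The trial has one arm, so its result is read against an outside figure. The Statistical analysis section cites a median of 11.5 months on first-line checkpoint inhibitors. In that setting no lesions have been irradiated under this trial, so there is nothing comparable to exempt. A more lenient event rule here would pass straight into the apparent benefit, with no control arm to absorb it.

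**Working it through.** **Step 1: the two rules side by side**

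| Patient's first event | Endpoint definition | Follow-up rule |
|---|---|---|
| New site | event | event |
| Growth of a previously stable lesion | event | event |
| Regrowth of an irradiated lesion | event | fits neither named category |
| Death | event | not mentioned |
| Criteria named | modified RECIST | RECIST 1.1 |

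The follow-up rule introduces its two categories with *i.e.*, which defines rather than illustrates. An irradiated lesion is not a new site. It was not stable before either, because lesions are irradiated for progressing. The two rules give different event dates when in-field regrowth comes first, and the same date when it does not (the difference in criteria aside).

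**Step 2: does the rest of the follow-up section settle it?** No.
- The sentence on trial completion governs participation, not the PFS event, and is qualified by *generally*. If in-field regrowth ended participation without a PFS event, the Kaplan-Meier analysis would censor the patient at the failure.
- The sentence on documenting growing lesions concerns recording, not endpoint status.
- Repeat local therapy is allowed, but its effect on PFS is not stated.

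**Step 3: size, if in-field failures were left out**

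The plan gives no figure of its own for this, so none can be reproduced. The sample size of 52 is not at issue here.

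Inputs:
- All-event median *m*: 11.5 months (Statistical analysis). Also 18.5 = 11.5 + 7, and 7 itself, because that section speaks both of an improvement of about 7 months and of detecting a median of 7 months.
- Local control at 12 months, *LC*: 93.5%, from a retrospective series of SBRT plus hyperthermia cited in the Discussion. 90% and 80% are assumptions without a source in the document.

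Assume constant hazards, with in-field failure independent of all other events. Ignoring and censoring in-field failures then give the same result:

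- all-event hazard = ln 2 / *m*
- in-field hazard = −ln(*LC*) / 12
- apparent median = ln 2 / (all-event hazard − in-field hazard)

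For *m* = 11.5 and *LC* = 0.935: 0.6931/11.5 = 0.06027; 0.06721/12 = 0.00560; 0.6931/0.05467 = 12.7 months.

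| True all-event median | LC 93.5% | LC 90% (assumed) | LC 80% (assumed) |
|---|---|---|---|
| 7 | 7.4 | 7.7 | 8.6 |
| 11.5 | 12.7 | 13.5 | 16.6 |
| 18.5 | 21.8 | 24.2 | 36.7 |

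Two checks on the input:
- A constant hazard from 93.5% implies 0.935² = 87.4% at 24 months, close to the 88.3% cited from the same series.
- The article does not say whether 93.5% is per lesion or per patient. If per lesion, three independent lesions give 0.935³ = 81.7% per patient, and 11.5 would read as 15.9 months. Up to 10 progressing lesions are allowed.

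**Step 4: effect on the test.** Take 11.5 months as the null median and as the true all-event median, and use a one-sample log-rank test at two-sided 0.05 with 12 months of uniform accrual and 24 months of further follow-up. The chance of a falsely favourable result would rise from 2.5% to about 7–9% at 93.5% local control and about 47–64% at 80%. The ranges cover 37 patients (52 × 0.85 × 0.85) to all 52, and two variants of the test.

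**The case against.** The strongest reply is that the follow-up section never says *only*. It states what happens when out-of-field progression occurs and does not say that in-field failure is excluded or censored. The formal definition, under its own heading, has no site restriction, and neither has the abstract. If that definition governs, there is no bias from this source. This stands. A reader might infer that the trial will leave in-field failures out and that its PFS is overstated, but the documents do not support that as a fact.

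The reply is also right on these points:
- A reader might infer that PFS uses a lesion-by-lesion modified RECIST. The per-lesion wording is in the eligibility criteria, and the endpoint definition says only modified RECIST. How the criteria are modified for follow-up may properly be left to the full protocol.
- The abstract's omission of death is condensation, not a third definition.
- The magnitude is illustrative. The 93.5% includes hyperthermia, and the Discussion itself warns of selection bias in these series. The 80% case, in which 5.1 of the 7 months would appear without any benefit, is an assumption. If out-of-field progression tends to follow soon after in-field failure, ignoring the latter delays the event by less.

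The reply does not remove the conflict. Both rules are stated in the article, so this is not detail left to a fuller document, and nothing says which rule prevails.

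**Conclusion.** The point holds as an inconsistency in the primary endpoint. The endpoint definition counts any further progression or death. The only text on what is recorded as the end of PFS at follow-up names progression outside the treated sites and uses a differently named set of criteria. Regrowth of an irradiated lesion is an event under one and falls outside the other.

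Upward bias is conditional on the follow-up wording being applied as written. At the one local control rate the document cites, the shift is about 1.2 months on a median of 11.5. It would be 2.0 months at an assumed 90% and 5.1 months at an assumed 80%. All of these rest on independent constant hazards, and the document does not fix the in-field failure rate for this trial. The conflict should be resolved before any PFS event is adjudicated for analysis.

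**What to change.** Amend Assessments and follow-up to match the Primary Endpoint text: PFS is the time from enrolment to first progression at any site, irradiated or not, or death from any cause. Name one set of response criteria for follow-up and use that name in both sections. Report out-of-field-only progression as a supportive endpoint, since it answers a separate and useful question about control of the remaining disease.

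The cost is wording in the protocol, the case report form guide and the analysis plan, with no extra scans. The downside is that reported PFS may be shorter than under the out-of-field rule.

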### Statistical analysis

As reviewed in the literature, first-line therapy with immune checkpoint inhibitors results in a mPFS of 11.5 months (12). Our study was designed with the expectation that we would observe a median PFS improvement of about 7 months with addition of SBRT. Assuming an enrolment time of 12 months and follow-up of 24 months, 15% drop out and another 15% of screen failure, a sample size of 52 patients will achieve 85% power at 0.05 significance level to detect a median PFS of 7 months based on a two-sided, single arm log-rank test.

PFS/OS will be estimated using Kaplan-Meier (KM) method and presented graphically. The cumulative incidences of change in systemic therapy and acute/late toxicity will be estimated using the Aalen-Johansen method, where mortality without events of interest will be treated as competing event. Univariate Cox proportional hazard models will also be conducted to examine the association of PFS/OS with patient and tumor characteristics of interest, such as age, sex and the number of oligoprogressive lesions treated, BRAF mutational status, and type of first-line systemic therapy. Similarly, the univariate Fine-Gray competing risk models will be applied to examine the association of time to change in systemic therapy/acute/late toxicity with the patient and tumor characteristics of interests. Multivariable analyses (MVA) will also be conducted to determine the association if applicable. The change in QOL scores at follow ups from baseline (before SBRT) will be analyzed using linear mixed-effect models and the change in scores of >10 points would be deemed a minimal clinically important difference. The other categorical secondary outcomes (e.g. Out of field response, AE) will be summarized using frequency counts and proportion.

An interim analysis will be conducted after the first 25 patients have been enrolled and followed for at least 6 months, to assess safety and early efficacy trends. If ≥30% of patients experience grade 3 or higher toxicities deemed related to SBRT at that time, early termination of the trial will be considered.

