**Clinical trial registration:**

## Introduction

Oligoprogression is characterized by the progression of cancer at a limited number of sites while majority of the disease remains stable on systemic therapy. Management of oligoprogressive disease may involve either switching systemic therapy or incorporating local treatments such as ablative stereotactic body radiotherapy (SBRT) or hypofractionated radiotherapy, while continuing or modifying the existing systemic regimen.

Prospective data supporting the benefit of SBRT for oligoprogressive cancers are scarce, and no trial has specifically evaluated patients with metastatic melanoma on immunotherapy (1–6). The recently published results of the CURB trial (randomized, phase II) clearly showed a four-fold improvement progression-free survival (PFS) with the addition of SBRT for patients with metastatic non−small cell lung cancer (mNSCLC). The clinical observation was accompanied by a corresponding decrease in mutant allele fraction of circulating tumor DNA (ctDNA) fraction in these patients after SBRT (7). Aside from CURB, another randomized phase 2 trial of SBRT for oligoprogressive cancers of mixed histologies was recently published. The STOP trial randomized patients to either SBRT or continuing standard-of-care (SOC) treatment, but was found negative (6). Thus far, there has been no trial investigating the effect of SBRT in oligoprogressive melanoma.

Melanoma incidence is increasing in Canada and worldwide (8–10). In 2022, an estimated 331,647 persons worldwide were diagnosed with melanoma, and approximately 58,645 persons died of the disease (11).

Although most patients are diagnosed with local disease and are cured with surgical resection, some patients develop or present with metastatic disease. Over the past decade, systemic treatment for metastatic melanoma has changed substantially. For example, the recently published 10-year survival outcomes from the Checkmate-067 trial demonstrated a 10-year mOS of 71.9 months for the combination of nivolumab and ipilimumab, and 37 months of nivolumab monotherapy. The 1- and 2-year PFS were about 50% and 45% respectively (12). For patients who progressed on immunotherapy, treatment options are limited. For patients harboring BRAF V600 mutations, a dual BRAF/MEK inhibitors are considered SOC, with a median PFS (mPFS) of about 10 months (13). Wild-type patients are treated with TIL (tumor infiltrating lymphocytes) therapy, resulting in a mPFS of 7 months (14).

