### Participant eligibility

Participants must be adults (age ≥18) with an ECOG performance status of 0-2, who have histologically confirmed metastatic melanoma. Patients must be receiving first-line systemic therapy and have demonstrated oligoprogressive disease on restaging evaluations. Oligoprogression is defined in this study as the presence of ≤10 sites of progressive disease (new or enlarging metastases) detected on imaging, while all other disease sites remain stable or responding to therapy. All progressive lesions must be extracranial (patients with only brain progression are excluded) and deemed safely treatable with high-dose radiotherapy.

Inclusion criteria include:

Metastatic melanoma on first-line systemic therapy: patients may be on anti-PD-1 monotherapy/combination (e.g. nivolumab ± ipilimumab), or on BRAF inhibitors.Oligoprogressive disease with ≤10 progressing lesions: progression is defined per modified RECIST 1.1 (≥20% diameter increase) or PERCIST (metabolic progression on PET) criteria for each lesion​. New lesions (≥5 mm) count toward the total of 10​. There is no upper limit on the total number of metastases in the body, as long as at most 10 are progressing.Amenable to SBRT: the locations of progression must be such that radiotherapy can be delivered without undue risk (assessed by a radiation oncologist). Lesions previously irradiated can be retreated if safe, and prior palliative radiation is permitted.Ability to consent and comply: patients must be willing and able to provide informed consent and comply with study procedures, including completion of quality-of-life questionnaires.

Exclusion criteria include:

Having >10 progressive lesions (widespread progression).Untreated or symptomatic central nervous system disease (patients with leptomeningeal disease are excluded​, as are those with unstable or symptomatic brain metastases).Pregnancy, or any serious comorbidity that would contraindicate radiotherapy (such as certain radiosensitive genetic conditions like ataxia-telangiectasia or scleroderma)​.Patients in whom prior radiation to a site precludes safe re-irradiation.Any circumstance that, in the investigator’s judgment, would interfere with the patient’s ability to participate or with the study results (such as significant psychosocial barriers to follow-up).

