In metastatic melanoma, ICIs have substantially improved outcomes. Combination therapy with nivolumab and ipilimumab has yielded 10-year OS of 43% (HR 0.53, 95% CI 0.44-0.65) (12). However, resistance develops in many patients, with progression often confined to limited sites. Management typically involves switching therapies (e.g., BRAF/MEK inhibitors in patients with a driver mutation, TIL therapy, or enrollment into a clinical trials). However, maintaining the same systemic treatment while controlling the progressive sites is an appealing option. This approach has been described in several retrospective trials. For example, a multicentre study from France evaluated the role of SBRT in metastatic melanoma patients. The study included 69 patients, of which 29 had oligo-progression. The 1-year PFS was 41%, the mPFS was about 6 months, and the median time to change treatment was 5 months (19).

In another retrospective study, 101 metastatic melanoma patients treated for oligo-progression with SBRT and hyperthermia were followed up for a median of 15.3 months. Although PFS was not reported, the 12- and 24- month local control rates were promising - 93.5% and 88.3% respectively (20). In another study of metastatic melanoma patients treated with immunotherapy, 36 patients were treated for oligo-progression with a loco regional approach. The mPFS was 32 months (21). An observational trial by Chicas-Sett et al. published in 2022 assessed the effect of SBRT and continuation of immune-checkpoint inhibition beyond progression, among patients with metastatic non-small cell lung cancer or melanoma. Of the 50 patients analyzed, 19 had melanoma, and 12 were evaluable. The mPFS for the melanoma sub-group was 21.2 months (22). While the results of these trials are certainly hypothesis generating, they are all retrospective in nature, and are thus subjected to selection bias. They have also incorporated slightly different combinations (for example hyperthermia combined with RT) and have measured different end-points. The CURB-Melanoma is a prospective trial that will assess survival outcomes as well as patient-centered outcomes such as QOL.

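### The primary PFS comparison is anchored to 11.5 months, a first-line checkpoint-inhibitor median, but trial PFS starts at enrolment in patients who have already progressed on first-line therapy

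*Protocol article*

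**What the plan says.** Statistical analysis gives a single benchmark: "first-line therapy with immune checkpoint inhibitors results in a mPFS of 11.5 months". The section then expects that "we would observe a median PFS improvement of about 7 months with addition of SBRT" and states that "a sample size of 52 patients will achieve 85% power at 0.05 significance level". The effect behind that figure is then worded differently: "to detect a median PFS of 7 months based on a two-sided, single arm log-rank test". It assumes 12 months of accrual, 24 months of follow-up, 15% drop-out and 15% screen failure. It does not say which median is the null.

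Under Study design, outcomes and end-points, PFS is "defined as time from enrollment to further disease progression (assessed by modified RECIST) or death from any cause". Participant eligibility states: "Patients must be receiving first-line systemic therapy and have demonstrated oligoprogressive disease on restaging evaluations". The same section admits patients on BRAF inhibitors as well as on anti-PD-1 therapy.

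The limitations paragraph of the Discussion concedes that there is no control arm, that oligoprogressive patients are probably a favourable subgroup, and that results are hypothesis-generating. It mentions neither the 11.5-month figure nor its time origin. It also says that a positive efficacy signal would justify a randomised trial.

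**The concern.** A first-line PFS interval ends at first progression on first-line therapy. Trial patients have had that progression before they can enrol, so the benchmark interval is over at about the point where the trial clock starts. The two quantities share the name PFS but describe different patients over different stretches of the disease. The benchmark also covers checkpoint inhibitors only, whereas eligibility is wider.

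The primary result would be read through this comparison, and the article ties the next step, a randomised trial, to a positive signal. If the reference does not describe PFS after oligoprogression without SBRT, a useful effect could be read as negative and ordinary natural history as positive.

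**Working it through.** **1. Does 11.5 months drive the sample size?** Inputs from Statistical analysis: accrual 12 months, follow-up 24 months, two-sided 0.05 (z = 1.960), power 85% (z = 1.036). Exponential PFS and uniform accrual are my assumptions. The probability of an observed event at hazard λ = ln 2/median is 1 − (e^(−24λ) − e^(−36λ))/(12λ).

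*Reading A: 7 months is an improvement, so 11.5 v 18.5.* Wu's one-sample log-rank formula is n = (1.960·σ̄ + 1.036·σ)²/ω².
- Event probability at 18.5 months: p1 = 0.672.
- Mean expected count per patient under the null hazard: p0 = 0.672 × 18.5/11.5 = 1.082.
- ω = p1 − p0 = −0.409.
- σ̄² = (p0 + p1)/2 = 0.877.
- σ², the variance of observed minus expected per patient under the alternative, is 1.111.
- n = (1.960 × 0.936 + 1.036 × 1.054)²/0.409² = 51.2, so 52.

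Simulated power at n = 52 is about 82–86%, depending on the variance form. This match leaves no room for attrition: dividing by 0.85 twice gives 71. The log-hazard-ratio formula gives 39.7 events and 60 patients.

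*Reading B: 7 months is itself a median, so 7 v 11.5.* Log-hazard-ratio formula:
- Events = (1.960 + 1.036)²/[ln(7/11.5)]² = 36.4.
- Event probability at 11.5 months = 0.832.
- n = 36.4/0.832 = 43.8, and 43.8/0.85 = 51.5, so 52.

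Both readings reach 52, so the arithmetic does not identify the null. In both, 11.5 months is one side of the contrast.

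**2. What post-progression figures does the article offer?**

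| Source in the article | Median PFS (months) | Why it is not a no-SBRT continuation cohort |
|---|---|---|
| Introduction, BRAF/MEK inhibitors after immunotherapy | about 10 | changed therapy |
| Introduction, TIL therapy ("resulting in a mPFS of 7 months") | 7 | changed therapy |
| Discussion, French SBRT series ("The 1-year PFS was 41%, the mPFS was about 6 months, and the median time to change treatment was 5 months") | about 6 | received SBRT; 29 of 69 oligoprogressive |
| Discussion, SBRT with continued checkpoint inhibition, melanoma subgroup | 21.2 | received SBRT; 12 evaluable |
| Discussion, locoregional treatment of oligoprogression | 32 | received local treatment |

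The span is about 6 to 32 months, on both sides of 11.5. No row describes patients continuing therapy without local treatment.

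**3. Illustration: how a test against 11.5 behaves.** One-sample log-rank with n = 52, exponential PFS, 40,000 simulated trials. O is the number of events and E = Σ(ln 2 × time at risk/11.5). A trial is positive if (E − O)/√E, or (E − O)/√((E + O)/2), exceeds 1.96. The range covers the two forms. The true medians are assumptions.

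| Assumed situation | True median (months) | Positive trials |
|---|---|---|
| SBRT doubles 6 months | 12 | about 4–5% |
| SBRT doubles 7 months | 14 | about 22–26% |
| No SBRT effect, favourable natural history | 15 | about 37–42% |

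The nominal rate in the favourable direction is 2.5%.

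**4. Would a lower null repair it?** With a natural median of 15 months and no SBRT effect, a null of 10 months is rejected in about 73–77% of trials and a null of 6 or 7 in nearly all. With a natural median of 11.5 and no effect, a null of 7 is rejected in 91–93%.

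**The case against.** The strongest reply has three parts.

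First, the article never names 11.5 months as the null, and it does not state the time origin of that figure. This stands. A reader might infer that 11.5 is proven to be the null; Reading B shows that it is not. The time origin is inferred from the wording, which presents the figure as the result of first-line therapy. Neither point removes the mismatch, because 11.5 enters the contrast under both readings.

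Second, the limitations paragraph already says that the SBRT contribution cannot be separated from natural history and that selection may prolong PFS. This concedes much of the false-positive risk, and Kaplan-Meier estimation is already planned. It does not concede that the reference belongs to an earlier interval of the disease. A single-arm trial can still use a matched historical reference, and this one does not.

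Third, no good reference exists. This also stands, and it limits the remedy. A reader might infer from the 6-, 7- and 10-month figures that the null should lie between 6 and 10 months. The documents do not support that: the article also reports 21.2 and 32 months, none of the five figures comes from patients continuing therapy without local treatment, and a lower null makes a false claim of benefit more likely if these patients do well anyway.

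The point does not depend on the unseen analysis plan, because the article itself states the benchmark and the sample-size basis.

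**Conclusion.** The mismatch is real and affects the only primary comparison. The 11.5-month figure and the trial endpoint differ in population and time origin, and the admitted drug classes are wider than the benchmark. Neither a positive nor a negative result against 11.5 months would show whether SBRT extends PFS after oligoprogression.

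The size cannot be fixed from the article. The percentages above are illustrations: they assume that 11.5 is the null, that 52 patients are analysed without drop-out, that PFS is exponential, and that the true medians are as listed. The exponential form is itself doubtful, because the Introduction gives 1- and 2-year first-line PFS of about 50% and 45%, whereas an exponential curve with median 11.5 months gives about 49% and 24%.

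A reader might infer that the test is tilted against SBRT, or in its favour. The documents support neither, because the direction depends on a no-SBRT median that they do not give.

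**What to change.** Do not test or interpret trial PFS against 11.5 months. Before the data are analysed, do one of the following:

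- **Keep a test.** Name and justify a null PFS counted from oligoprogression or enrolment in patients continuing systemic therapy, with a sensitivity range. State the alternative, and give the power of 52 patients against that null.
- **Drop the test.** If no such reference can be defended, make the Kaplan-Meier median and the 6- and 12-month PFS with 95% confidence intervals the primary result. Replace the power statement with the precision expected from 52 patients.

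Do not take 6–10 months as the null by default. In either case, reconcile the two 7-month statements, so that it is clear whether 7 months is a gain or a median, and say how the two 15% allowances enter the 52. Add the reference mismatch to the limitations paragraph.

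The cost is new wording and a repeated power or precision calculation. The downside is that any post-progression reference is less certain than a first-line trial figure, and the stated 85% power may change or have to be dropped.
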